#### Foreseeable SAEs relating to known complication(s) of prematurity

Any serious event that is deemed by the investigator to be a known complication of prematurity at that gestational age should not be reported as an SAE but should be recorded in the infant’s medical notes, as per usual practice. They do not require reporting by trial centres as SAEs unless considered that they may be causally related to the allocated pathway of care.

#### SAEs which require expedited reporting

Any other SAEs not detailed above are classed as unforeseeable SAEs and must be reported.

#### Reporting procedures for SAEs

SAEs requiring expedited reporting must be reported as soon as possible after the site becomes aware of the event being defined as serious. The relationship of each adverse event to the allocated pathway of care will be determined by a medically qualified individual, and all SAEs labelled possibly, probably or definitely will be considered as related to the allocated pathway of care. An SAE that is deemed to be related to the allocated care pathway will be assessed by the CI or the Australian CI (or other appropriate delegate) to determine whether the event is expected or unexpected in terms of the current known safety profile of the allocated pathway of care. All related and unexpected SAEs will be submitted to the sponsor and the Research Ethics Committee (REC) that gave a favourable opinion of the trial within 15 days of the CI becoming aware of the event and also to the DMC, sponsor and the R&D offices.

### Participant timeline {18}

**Table Tabc:** 

	**Period**						
	**Enrolment**		**Post-randomisation**				**Close-out**
**Timepoint**	**After birth**	**After eligibility confirmed**	**Day 1**	**Day 2**	**Day 3**	**etc**	**Discharge from neonatal unit or 44 + 0 gestational weeks + days**
Enrolment							
Eligibility screen	X						
Opt-out consent	X						
Randomisation		X					
Baseline data		X					
Intervention/comparator							
*Routine* or *no routine* measurement of gastric residual volumes			X	X	X	X	
Assessments							
Daily feeding log			X	X	X	X^a^	
Late-onset infection and gut signs						X^b^	
Data at discharge or **44 + 0 gestational weeks + days**							
Clinical data^c^							X^d^

^a^Daily feeding logs until day 14, and then until the infant achieves full enteral feeds (at least 145 ml/kg/day where this is considered full enteral feeds, or where breastfeeding and any additional milk is considered equivalent to full enteral feeds) for 3 consecutive days, or reaches 44 + 0 gestational weeks + days

^b^Each episode of microbiologically confirmed or clinically suspected late-onset invasive infection, or if an infant has received at least 5 days of treatment for gut signs, if they are transferred with gut signs, or if they have died from gut signs, should be reported throughout the treatment period until hospital discharge

^c^Clinical data is collected via the electronic case report form or from routinely recorded clinical data where applicable

^d^If infant is withdrawn from the trial and parent/carer has asked for no further data collection, the transfer/discharge form can be completed at the time of withdrawal for data up until point of withdrawal

### Sample size {19}

The original planned sample size for this trial is 7040 infants (3520 per arm) individually randomised in neonatal units in the UK and Australia. Multiple births will be randomised to the same arm. Following consultation with trial oversight committees recruitment will continue until the planned end date of 28 February 2026, recognising that this may result in a higher final sample size.

#### Time to full enteral feeding

From the National Neonatal Research Database (NNRD), UK population level neonatal data, the overall mean number of days to full enteral feeding in infants born less than 34 weeks of gestation is 9.4 (standard deviation 10.8) days. To detect a 1-day reduction in the time taken to reach full enteral feeding (important clinically and important to parents) with 90% power and a two-sided 5% significance level, a sample size of 5088 infants (2544 per arm) is required (assuming a standard deviation of 11 days). Based on data from other feeding trials [24, 25] we anticipate 30% multiple births and an intracluster correlation coefficient (ICC) for multiple birth sets of 0.3, leading to an inflation of the sample size by 6% to account for the correlation in outcomes within multiple birth sets [24, 25]. A small level of crossover in the ‘no routine measurement’ group is anticipated, with some measuring of gastric residuals occurring outside of the protocol guidelines; to allow for 10% crossover (non-adherence), the sample size has been inflated by 24% to obtain the same level of power [26]. Applying these inflation rates and assuming a 5% attrition rate to discharge, the total number of infants required is 7040 (3520 per arm).

#### Moderate to severe NEC

From the NNRD the incidence of significant NEC (requiring surgery, leading to death or recorded as part of the National Neonatal Audit Programme) is 3%. With a total sample size of 7040 and a control group event rate of 3%, the trial would have 92% power to detect a non-inferiority margin of 1.5% in the treatment risk difference, with a one-sided 2.5% significance level: non-inferiority can be claimed if the upper bound of the confidence interval of the treatment effect does not exceed 1.5%. These figures also allow for 10% crossover and 5% attrition. The inflation factor to account for the correlation in outcomes within multiple birth sets for NEC is 1% assuming a lower ICC of 0.05.

#### Recruitment {20}

The trial is designed to be pragmatic and low burden through simple, streamlined opt-out consent and minimal data collection. Many sites will be involved, including sites not commonly involved in neonatal trials, for example, smaller non-tertiary units. We plan to enrol from all four nations of the UK and in three Australian states.

## Assignment of interventions: randomisation

### Sequence generation who will generate the sequence {21a}

A Senior Trials Programmer at the Clinical Trials Unit (CTU) will write the web-based randomisation program and hold the allocation codes. Randomisation of infants to either the no routine measurement of gastric residual volumes or the at least 6-hourly measurement of gastric residual volumes will use a 1:1 allocation ratio.

### Sequence generation: type of randomisation {21a, 21b}

The randomisation program will use a probabilistic minimisation algorithm. To ensure balance between the randomised groups, minimisation criteria will comprise: randomising hospital, multiple births, and week of gestational age at birth.

Infants that are part of a multiple birth set (twins or higher order multiples) will be randomised as a multiple: they will all be allocated to the same care pathway. This is based upon feedback from parent representatives, parent organisations and research involving parents and ex-preterm twins [27].

### Allocation concealment mechanism {22}

Infants will be randomised using an online secure central randomisation service to ensure allocation concealment.

### Implementation {23}

Staff at recruiting sites will log into the randomisation website using a unique centre login to randomise participants. The system will confirm eligibility, allocate a unique neoGASTRIC Study ID, and then assign the infant to one arm of the trial.

## Assignment of interventions: blinding

### Who will be blinded {24a}

Because it is not possible to mask the different care pathways, parents and clinicians (including treating clinicians and clinicians recording outcomes) will be unblinded to the allocated care pathway.

A Blinded Endpoint Review Committee (BERC) will undertake a blinded assessment of key clinical outcomes—NEC, focal intestinal perforation, late-onset infection and, where appropriate, time to full feeds.

**Table Tabd:** 

Individual	Blinding status	Comments
Parents and infant	Not blinded	Not possible due to the nature of intervention. Parents will be informed which arm of the trial they have been randomised to
Principal Investigator (PI) and other site staff	Not blinded	Not possible due to the nature of intervention. Following randomisation, an email will be sent to the PI and/or other site staff (as agreed locally) confirming allocation
Chief Investigator (CI) UK and Australia	Not blinded to individual infants Blinded to all aggregate data	Not possible for individual infants at their site due to the nature of intervention The CIs also act as PIs for their site—see comments for PIs above, The CI will remain blinded to treatment allocation overall. CIs will not be blinded for infants when involved in evaluating a serious adverse event (SAE)
Database programmer	Not blinded	The database programmer will be responsible for the management of the randomisation database and will also have access to unblinded datasets within the trial database
Trial and data management staff	Not blinded to individual infants Blinded to all aggregate data	Trial and data management staff will have access to unblinded individual records within the clinical database as this is an unblinded study
Trial statistician	Not blinded	The trial statistician will draft the statistical analysis plan before they receive the first unblinded dataset. Thereafter, on request, the trial statistician will have access to the unblinded dataset as this is an unblinded study
Members of the BERC	Blinded	Members of the BERC will assess the relevant Case Report Forms (CRFs) and (if necessary) anonymised medical notes

### How will blinding be achieved {24b]

N/A—this is not a blinded trial.

### Procedure for unblinding if needed {24c}

N/A—this is not a blinded trial.

### Data collection and management

#### Plans for assessment and collection of outcomes {25a}

The majority of trial data will be collected using electronic CRFs and entered directly into the secure OpenClinica Clinical Database Management System (CDMS). The individual participant data will be identified by a study participant number only.

Necrotising enterocolitis, intestinal perforation and neonatal infection will also be assessed by a BERC. BERC reviewers will be medical professionals who are experts in the conditions for which endpoint data is being collected for analysis. See Additional file 4 for more details on the BERC review charter.

### Plans to promote participant retention and complete follow-up {25b}

The Project Management Group (PMG) will remotely monitor the completeness of study documentation and maintain regular contact with all sites to ensure the accuracy and completeness of all study documentation during the infants’ participation in the study. For infants who discontinue participation or where there is a deviation from protocol after the point of randomisation, sites will be asked to record the reasons for this and to continue data collection, where possible, so they can be included in the analysis of outcomes, according to the intention to treat analysis principle.

To support participant retention, several strategies will be implemented throughout the trial. All recruiting sites will receive training at setup, with ongoing support provided via the study website and through direct contact with the trial coordinating team as needed. The Parent Information Sheet (PIS) will be translated into seventeen languages other than English to help make the trial information accessible to families from diverse backgrounds. If an infant is discontinued from the allocated trial pathway but remains in the trial, data collection will continue. If an infant withdraws from the trial completely, data collected up to the point of withdrawal will be used for analysis. Monthly reports on missing data and outstanding CRFs will be shared with sites.

Communication between recruiting sites and Continuing Care Sites (CCSs) will be actively facilitated by the trial coordinating team at the National Perinatal Epidemiology Unit (NPEU) CTU, to support continued data collection following any infant transfers, including to non-CCSs. To maintain engagement, the trial will include structured retention and communication strategies, including staff recognition and family-facing materials. Monthly informal meetings with the coordinating team will provide sites with an opportunity to ask questions, exchange ideas, share key learnings and troubleshoot issues collaboratively.

### Data management {26}

Trial data will be recorded primarily through CRFs using the OpenClinica system from source documents.

OpenClinica is a CDMS used by the NPEU CTU to undertake the management, storing and curation of clinical data. The application is hosted in the UK by an ISO 27001:2013 (Information Security) accredited third party. Updates or new versions of the application are implemented by OpenClinica.

CRF entries will be considered source data if the CRF is the site of the original recording. Clinical data will be entered into a validated database, with validation checks for accuracy. Participant names and identifiable information will be stored in a separate administrative database. Electronic and paper records will be stored securely, with restricted access to authorised personnel. Electronic files will be stored on a secure server, with regular backups and restricted entry. Archiving will follow local guidelines for at least 25 years in the UK and in Australia until the youngest participant reaches the age of 33, with a review of further archiving needs based on data protection laws.

At the end of the trial, all participant data will be transferred to Imperial College London for long-term follow-up, in compliance with data sharing agreements. Trial data for Australian infants only will be transferred securely to Monash University in Australia.

The detailed Data Flow is available in Additional file 3.

### Confidentiality {33}

The trial will adhere to strict data privacy regulations, including the General Data Protection Regulation (GDPR) and Data Protection Act 2018. All documents will be stored securely at the NPEU CTU and accessible only to authorised trial staff. Personal identifiers and trial data will be stored in a separate database linked by the infant’s trial number. After the trial is completed and reports are published, data will be archived in a secure location with controlled access.

### Process evaluation sub-study {12, 20, 27d}

#### Design

The trial includes a mixed methods process evaluation to evaluate the UK pilot phase trial processes, to inform the successful conduct of the ongoing neoGASTRIC trial. Involving site observations, surveys, interviews and focus groups with parents of eligible infants and site staff, the objectives are to review: (1) gastric residual volume measurement processes and protocol adherence, (2) acceptability of not routinely measuring gastric residual volumes, (3) experience of recruitment and opt-out consent, clinical equipoise and (4) staff training needs to inform ongoing trial conduct and training. Topic guides and questionnaires were developed using trial feasibility findings [28].

#### Recruitment and sampling

The first four UK sites open to recruitment will be invited to take part in the process evaluation. Staff will invite parents of the first 20 eligible infants, including those who ‘opt out’ to complete a questionnaire before leaving hospital and/or to register interest in participating in an interview with a University of Liverpool researcher within a month. Staff will be invited to complete a questionnaire relating to recruitment and trial processes for the same 20 infants and take part in an online focus group after 4–6 months of trial recruitment. Site observations will take place at participating sites during the pilot phase.

Based on previous studies, we anticipate interviewing 15–25 parents and conducting 2–4 focus groups to reach information power [29, 30]. We anticipate around 80 parents and staff questionnaires related to 20 infants per site.

#### Analysis

Process evaluation data analysis will be informed by Normalization Process Theory [30]. Digital audio recordings will be transcribed verbatim by a transcription company (UK Transcription, Brighton, UK), checked and anonymised before being imported into NVivo V.14 software for organising and coding. Reflexive thematic analysis will be used for qualitative data, whilst questionnaire data will be inputted into Statistical Product and Service Solutions (SPSS), and descriptive statistics will be used.

## Statistical methods

### Statistical methods for primary and secondary outcomes {27a}

Statistical analyses will be conducted according to a pre-specified statistical analysis plan (SAP), which will be available in a separate document. The SAP will provide detailed information on the methods used to analyse the primary and secondary outcomes, including any adjustments for covariates.

The *routine at least 6-hourly measurement of gastric residual volumes* group will be used as the reference group in all analyses.

#### Primary outcome

The mean, standard deviation, median and interquartile range will be presented by randomised group. For the comparative analysis, a mixed linear regression will be fitted, with mean differences and 95% confidence intervals presented where model assumptions are satisfied. If normality assumptions are not met, quantile regression models will be used with median differences and 95% confidence intervals presented. The model will be adjusted for minimisation factors, which include recruiting centre, gestational age at birth, and whether the infant is one of a multiple birth. Centre will be treated as a random effect, while all other factors will be treated as fixed effects. Correlation between recruited siblings from multiple births will be accounted for by nesting the ‘multiple’ cluster within centre, where technically possible. Both crude and adjusted effect estimates will be presented, but the primary inference will be based on the adjusted estimates.

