### Outcomes {16}

**Table Tabb:** 

**Primary outcome**	**Primary outcome measure**	**Time point**
Primary outcome (superiority outcome)	Time (in days) from birth to reach full milk feeds for 3 consecutive days (at least 145 ml/kg/day where this is considered full enteral feeds, or where breastfeeding and any additional milk is considered equivalent to full enteral feeds)	Up to discharge home or 44 + 0 gestational weeks + days (whichever is sooner)
**Secondary outcomes**	**Secondary clinical outcome measures**	**Time point(s) of evaluation**
Key secondary outcome (non-inferiority outcome)	NEC: modified Bell’s stage 2 or greater [15], evaluated by Blinded Endpoint Review Committee (BERC)	Up to discharge home or 44 + 0 gestational weeks + days (whichever is sooner)
Other secondary outcomes	• Severe NEC, confirmed at surgery or leading to death, evaluated by BERC	
	• All-cause mortality	
	• Focal intestinal perforation, evaluated by BERC	
	• Gastrointestinal surgery	
	• Late-onset infection (> 72 h after birth): microbiologically confirmed [19, 20] or clinically suspected infection [21] evaluated by BERC	
	• Duration of neonatal unit stay, in days, including all levels of care	
	• Duration of any parenteral nutrition, in days	
	• Duration with a central venous line in situ, in days	
	• Weight for gestational age standard deviation score	
	• Head circumference for gestational age standard deviation score	
	• Duration of invasive ventilation, in days	
	• Chronic lung disease: receiving oxygen or respiratory support at 36 weeks’ corrected gestational age	
	• Retinopathy of prematurity: treated medically or surgically [22]	
	• Brain injury on imaging: intraventricular haemorrhage grade 3 or 4 and/or cystic periventricular leukomalacia [23]	
	• Any vomiting resulting in feeds being withheld	Up to 14 days from randomisation
	• Number of days feeds withheld at least once	Up to 14 days from randomisation
	• Total number of hours feeds withheld	Up to 14 days from randomisation
	• Breastfeeding	At discharge home or 44 + 0 gestational weeks + days (whichever is sooner)
	• Receiving maternal breastmilk	
**Costing study**	• Number of gastric residual volume measurements	Up to 14 days from randomisation
	• Abdominal x-ray investigations^a^	Up to discharge home or 44 + 0 gestational weeks + days (whichever is sooner)
	• Antibiotic use and surgery for NEC or focal intestinal perforation	
	• Healthcare costs^b^	

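### A normality check decides whether the primary estimate is a mean or a median difference, but the sample size is justified only for a mean

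*Protocol article*

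**What the plan says.** The outcomes table of the protocol article defines the primary outcome as "Time (in days) from birth to reach full milk feeds for 3 consecutive days".

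Under Statistical methods, Primary outcome, the first-choice model is a mixed linear regression giving a mean difference, conditional on its assumptions being satisfied. The fallback is: "If normality assumptions are not met, quantile regression models will be used with median differences and 95% confidence intervals presented". The model adjusts for centre (random), gestational age and multiple birth, and the primary inference rests on the adjusted estimate. Sibling correlation is to be handled by nesting the multiple-birth "cluster within centre, where technically possible".

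Under Sample size, Time to full enteral feeding, national data give a mean that "is 9.4 (standard deviation 10.8) days". The aim is "To detect a 1-day reduction in the time taken to reach full enteral feeding". The SD entered in the calculation is 11 days, and the base requirement reads: "with 90% power and a two-sided 5% significance level, a sample size of 5088 infants (2544 per arm) is required". Inflation for multiple births, crossover and attrition brings the total to 7040. The article gives no target difference or power for a median.

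**The concern.** A mean difference and a median difference answer different questions. Under the rule as written, the residuals seen at analysis decide which one carries the primary conclusion. The article's own mean and SD make the median the likely outcome of that rule, yet the trial was sized for the mean. The headline result could then be a quantity for which no target was set and no power calculated. The 1-day benefit described as important clinically and to parents would not be the thing tested.

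**Working it through.** **1. The stated sample size is for a mean.** Inputs: difference 1 day, SD 11, two-sided 5%, 90% power, 1:1 allocation.
- n per arm = 2 × (1.960 + 1.282)² × 11² / 1² ≈ 2543, or 5086 in total. The article states 5088.
- 5088 × 1.06 × 1.24 / 0.95 = 7039.6. The article states 7040.
- Effective n per arm after attrition and clustering = 7040 × 0.95 / 1.06 / 2 ≈ 3155. With 10% crossover the difference is diluted to 0.9 day. Its standard error is 11 × √(2/3155) = 0.277, which gives 90% power.

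The figures reproduce as a two-sample comparison of means.

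**2. How likely is the switch?** The outcome cannot fall below zero.
- Normal(9.4, 10.8): P(below 0) = Φ(−9.4/10.8) = Φ(−0.870) = 19.2%. The marginal distribution is therefore clearly skewed.
- The model assumption concerns residuals given the covariates. To hold the share below zero to 2.5% at the overall mean, the residual SD must be at most 9.4/1.96 = 4.8 days. The covariates would then have to explain 1 − (4.8/10.8)² ≈ 80% of the variance.
- For infants with a predicted time of 6 days (an assumption), the limit is 6/1.96 = 3.06 days, or about 92% of the variance.

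Non-normal residuals are very likely, but this does not prove them.

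**3. What a 1-day mean reduction becomes on the median.** The article gives only a mean and an SD, so the shapes are assumed. Two non-negative distributions are matched to 9.4 and 10.8.
- Lognormal: σ² = ln(1 + (10.8/9.4)²) = 0.842; median = 9.4/√2.320 = 6.17 days; skewness about 5.0.
- Gamma: shape (9.4/10.8)² = 0.758; median 5.72 days; skewness about 2.3.

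The size of the median difference then depends on the form of the effect:
- Proportional effect (factor 8.4/9.4): 6.17/9.4 = 0.66 day (lognormal) or 5.72/9.4 = 0.61 day (gamma).
- Pure shift: 1 day.
- Effect confined to the slowest quarter: a 4-day reduction in those infants gives 0.25 × 4 = 1 day on the mean. In both distributions these infants stay above the median (lognormal 75th percentile 11.4 days, less 4 = 7.4, against a median of 6.2), so the median difference is 0.

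**4. Power for the median.** This uses continuous time, no covariate adjustment, 3155 per arm and 10% crossover. The standard error of the difference is √2 / (2 f(m) √n), where f(m) is the density at the median.
- Standard error: 0.179 (lognormal), 0.250 (gamma).
- Proportional effect: Φ(0.9 × 0.657/0.179 − 1.96) = 91% (lognormal); Φ(0.9 × 0.609/0.250 − 1.96) = 59% (gamma).
- Pure shift: over 99% (lognormal); 95% (gamma).
- Slowest-quarter effect: about 5%, the significance level alone.

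**5. Recording in whole days.** If times are whole days, which the unit and the daily feeding log suggest but do not state, sample medians sit on whole-day values. A true median difference of 0.6 to 0.7 day will then usually be estimated as 0 or 1 day in an unadjusted comparison.

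**The case against.** The fallback is pre-specified, and the primary objective speaks of reducing time without naming a mean, so a median does not contradict it. Mean, SD, median and interquartile range are shown by arm whichever model is used. Detailed methods are left to an SAP that is not shown. All of this is fair, and the lack of a stated normality criterion in the article is not counted against it. But an SAP that defined the check would still be carrying out the published switch, and by-arm summaries are not the primary inference.

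Three stronger readings are tempting, and the documents do not support them.
- *The switch is certain.* The 19.2% describes the marginal outcome, whereas the assumption applies to residuals after adjustment for gestational age, multiple birth and centre.
- *The switch destroys power.* Step 4 runs from about 5% to over 99%. Simulations of an unadjusted whole-day median under a proportional effect, with 3344 per arm (3520 × 0.95) and no crossover, reject in anything from about 0% to 31% of trials depending on shape and rounding rule. With unrounded times the figure is roughly 75% to 99%. None of these is the planned adjusted test, so no single figure can be attached to the plan.
- *Siblings will be analysed as independent.* The article commits to accounting for sibling correlation. The qualifier attaches to how that is done by nesting, and clustered errors for quantile regression may be in the SAP. Even if clustering were ignored, a design effect of 1.06 would give a type I error of 2Φ(−1.96/√1.06) = 5.7%.

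**Conclusion.** The concern holds in a limited form and should be fixed before analysis. The primary estimand is left to a data-dependent check, and the sample size supports only one of the two possible answers. The other answer is the likelier one, given a non-negative outcome whose SD exceeds its mean. If the switch occurs, the 1-day target corresponds to a median difference anywhere from 0 to 1 day, and the stated 90% power no longer describes the test. Power could be higher or lower. The mismatch between estimand and sample size follows from the article's own text and figures. The median values and their power rest on assumed lognormal and gamma shapes, assumed effect forms and an unadjusted approximation. The coarseness point rests on whole-day recording.

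**What to change.** Delete the normality switch. State that the primary estimate is the adjusted mean difference in days from the linear mixed model, whatever the residual distribution. Use standard errors that are robust to non-normality and clustered at least at multiple-birth-set level. With about 3155 effective infants per arm, inference on a mean does not need normal residuals. Report the quantile-regression median difference as supportive, with standard errors that respect multiple-birth sets.

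The cost is wording in the protocol and SAP. The article says the SAP will be finalised before follow-up ends, which gives a natural point for the change. No new data or infants are needed, and 7040 stands. The small downside is that a mean is more sensitive to very long times, which the supportive median addresses.
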